Activation is defined as the capacity and ability to manage one’s personal condition, collaborate with the health provider to maintain one’s own health and wellbeing, access adequate and high-quality care, and prevent health deterioration (43). The Patient Activation Measure (PAM) allows evaluation of the self-knowledge, motivation, and aptitude to manage one’s own health (43). Activation is a tool that allows individuals to reach and maintain healthy lifestyles, and optimize their quality of life (44). Higher activation levels are associated with people with better self-healing capacity, better health status, and lower use of health services (45, 46).

Health literacy refers to the health knowledge of the population, their motivation and individual abilities to understand and make decisions related to the promotion and maintenance of their health (47). Adequate health literacy levels have been associated with healthy lifestyle behaviors, such as eating five servings of fruit and vegetables per day or being a non-smoker-regardless of age, educational level, sex, ethnicity, or income (48, 49). Low health literacy can hinder health self-care and be related to a higher incidence of chronic diseases (50). From a health and social perspective, the improvement of health literacy is an unavoidablechallenge.

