### Sample size

2.3.

The sample size was computed using the GRANMO sample size calculator. We considered the estimation of the relative risk (RR) for a cohort study (using the Poisson approximation), with 10 years of follow-up and a rate of loss to follow-up of 30%, accepting an alpha risk of 0.05 and a beta risk of 0.2 in a bilateral contrast. The incidence of morbidity was considered as the main dependent variable and was around 60% in a previous analysis with 10.14 years follow-up (2). Health literacy was considered as the main independent variable. According to the questionnaire HLS-EU, 58,3% of the Spanish population has an inadequate or problematic level of health literacy (47). Low levels of health literacy have been linked to poorer physical and mental health outcomes, increased use of health services (68–70), and higher all-cause mortality (71, 72). Taking all these parameters into account, a sample of 3,083 persons is required, 1,793 in the exposed group (inadequate or problematic health literacy, HLS-EU-Q16 score between 0 and 12) and 1,290 in the non-exposed group (HLS-EU-Q16 score between 13 and 16). The sample size has been calculated to detect a minimum RR of 1.1 at 10 years, and will allow the detection of a minimum RR of 1.2 at 5 years, which is lower than some of the figures reported in the literature (73).

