The evaluation of the participants’ mental health will also include the following: a questionnaire on the generalized anxiety disorder (GAD-7) (87), which evaluates the presence of symptoms; examination of the diagnostic criteria for major depression, using the PHQ-9 (88); and estimation of the risk of depression (89), in participants with no diagnosis of a major depressive episode.

We will evaluate the several lifestyles: adherence to the Mediterranean diet, assessed with the PREDIMED (82) and PREDIMED plus (83) questionnaires; type of diet, determined by asking the participants if they follow any specific diet (e.g., vegetarian, vegan); level of physical activity, assessed with the International Physical Activity Questionnaire (84); smoking habit, measured with the 4-question scale adapted from the WHO MONICA study (90); alcohol consumption, considering the total units during the past week and a question on the monthly frequency of excessive consumption (binge drinking) over the past year; and sleep, evaluated using the Pittsburgh Sleep Quality Index (85), the overall number of sleeping hours, usual bedtime, and waking-up time.

The quality of life will be determined using the EUROQol 5D-5L health questionnaire (86), and a question on self-perceived well-being. Finally, the utilization of health services for the last 12 months previous to inclusion into the study will be extracted from electronic health records. Where the research team may have no access to electronic health records, the utilization of health services will be assessed with a survey answered by the participants. The items will enquire on the number of visits (to the emergency department, primary care, and other specialties), hospital admissions, diagnostic tests, and pharmacological treatment (medication, dose, total daily dose, and duration).

Additionally, we will consider the following groups of covariates: sociodemographic, social, functional capacity, and stress level.

We will register the following sociodemographic variables: date of birth, sex, sex orientation, and gender identity (SOGI questions), marital status, nationality, and employment status. We will also consider occupational social class, defined with the educational level and occupation. Participants will answer questions on employment conditions (six items), domestic and care work (six items), income level and economic situation (four items), and housing and material situation.

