### Statistical analysis

2.6.

The statistical analysis will include a descriptive analysis. Percentages of the categorical variables will be calculated for each AACC. Continuous variables with a normal distribution will be described with the mean (standard deviation, SD); otherwise, the median (first and third quartile) will be used. The analyses will be stratified by sex. Bivariate analyses will be performed using the *t*-test for independent samples, or the Mann–Whitney test when required, to analyze continuous variables; and the Chi-squared test for proportions.

Objective one will analyze the incidence of morbidity, defined as the onset of any new condition out of the 17 considered. To this end, a Cox model will be built for each independent variable, and adjusted for the above-mentioned covariates. Potential heterogeneity between AACC will be estimated by introducing random effects in the model. Sensitivity analyses will examine loss to follow-up rates. Objective two will analyze the incidence of the rest of the dependent variables (except incidence of morbidity) using also Cox models, one for each of the six independent variables, adjusted for the covariates. We will calculate the incidence of all-cause mortality and its Kaplan–Meier, stratified by the categorical variables and AACC. Potential heterogeneity will be estimated, and sensitivity analyses performed as in objective one.

Before obtaining the follow-up information at 5 and 10 years, we will describe and analyze the gathered data at baseline. To this end, general linear multilevel models will be used to examine the association of the dependent variables (lifestyles, quality of life, and use of services), with the six independent variables, adjusted for the registered covariates (age, sex, occupational social class, social capital, functional capacity, and stress level). Potential disparities between AACC will be captured by including random effects in the models.

Statistical significance will be considered at *p*-values < 0.05. The analyses will be carried out using the Statistical Package for the Social Sciences (SPSS) version 26.0, and the R-software.

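### Educational level is adjusted for only as a component of occupational social class, which may leave residual confounding by education in the health-literacy association

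*Protocol article*

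**What the plan says.** In the protocol article, Variables (2.4), education appears among the sociodemographic covariates only through a composite: "We will also consider occupational social class, defined with the educational level and occupation". The number of classes and the weight given to education are not stated. The same paragraph also lists employment, domestic work, income and housing items.

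Statistical analysis (2.6) has two kinds of model:

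- The baseline multilevel models are "adjusted for the registered covariates (age, sex, occupational social class, social capital, functional capacity, and stress level". This list is explicit and has no education term.
- The Cox models for morbidity and the other outcomes are adjusted by reference back to the covariates already described, that is, the wider set in 2.4. Education has no separate entry there.

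Study objectives and hypotheses (1.1) asks whether each aptitude is independently associated with morbidity. Sample size (2.3) names health literacy as the main independent variable. The Introduction counts education among the determinants of health, and reports earlier literacy associations that held regardless "of age, educational level, sex, ethnicity, or income (48, 49".

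**The concern.** People in the same occupational class can differ in schooling. If, within a class, those with less schooling more often have low health literacy and also have more morbidity by other routes, the literacy coefficient takes up part of the effect of education. A test of independent association would then partly be a test of education. Participants are 35 to 74 years old, so schooling mostly precedes the baseline literacy measurement. It is therefore better seen as a confounder than as a step on the path from literacy to disease. The target effect is small (a relative risk of 1.1), so even modest residual confounding could matter for how the main result is read.

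**Working it through.** **1. The plan's own figure.** Inputs from Sample size (2.3):

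- "accepting an alpha risk of 0.05 and a beta risk of 0.2 in a bilateral contrast";
- "with 10 years of follow-up and a rate of loss to follow-up of 30" per cent;
- morbidity incidence that "was around 60% in a previous analysis with 10.14 years follow-up";
- "58,3% of the Spanish population has an inadequate or problematic level of health literacy";
- target relative risk 1.1.

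Take p0 = 0.60, p1 = 0.66 and k = 1,793/1,290 = 1.39. The log relative risk formula with binomial variance is

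n0 = (1.960 + 0.842)² × [(1 − p1)/(k·p1) + (1 − p0)/p0] / (ln 1.1)² = 7.849 × (0.3706 + 0.6667)/0.009084 ≈ 896.

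Dividing by 0.70 gives 1,280 non-exposed and about 3,060 in total. A two-proportion formula with continuity correction gives 3,073. Both are within 1% of the article: "a sample of 3,083 persons is required, 1,793 in the exposed group". A pure Poisson variance gives about 8,000 and does not reproduce it; that is a separate matter. The covariate question leaves the sample size unchanged.

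**2. Simulation with no literacy effect.** From the article: 3,083 × 0.70 ≈ 2,158 people, 10 years, baseline hazard −ln(0.40)/10 = 0.0916 per year (60% incidence), about 58 to 59% with low literacy, two-sided 5% test.

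Assumed, because the article gives no values: three levels each of education and occupation, latent correlation 0.6, and no other covariates. The odds ratio (OR) for low literacy and the morbidity hazard ratios (HR) are per level of lower education or occupation.

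Four class rules were compared with education and occupation as separate terms:

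- Sum, 5 classes: education plus occupation.
- Sum, 3 classes: the same sum, grouped.
- Mainly occupational: occupation, with the top level split by degree.
- Two classes: middle or higher occupation, or highest education, against the rest.

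There were 1,500 replicates per cell; Monte Carlo SE = √(0.05 × 0.95/1,500) ≈ 0.6 points. Cells show the rejection rate and, in brackets, the average literacy HR (true value 1).

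| Education HR / occupation HR / literacy OR | Sum, 5 classes | Sum, 3 classes | Mainly occupational | Two classes | Separate terms |
|---|---|---|---|---|---|
| 1.00 / 1.00 / 1.8 | 4.6% (1.002) | 4.5% (1.002) | 4.9% (1.002) | 4.7% (1.002) | 4.9% (1.001) |
| 1.00 / 1.15 / 1.8 | 5.5% (0.986) | 4.9% (0.990) | 4.3% (0.999) | 4.3% (1.001) | 4.2% (0.999) |
| 1.10 / 1.10 / 1.8 | 5.5% (1.004) | 5.7% (1.009) | 7.4% (1.026) | 8.1% (1.030) | 5.0% (1.004) |
| 1.15 / 1.00 / 1.8 | 6.2% (1.012) | 6.5% (1.016) | 9.0% (1.031) | 9.9% (1.035) | 5.9% (0.999) |
| 1.15 / 1.15 / 1.8 | 5.1% (1.000) | 4.9% (1.008) | 9.3% (1.034) | 10.5% (1.038) | 5.0% (1.000) |
| 1.20 / 1.10 / 2.2 | 4.2% (1.014) | 6.0% (1.025) | 16.1% (1.062) | 18.5% (1.067) | 3.9% (1.002) |

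With separate terms the error is nominal within noise throughout. With no education effect it is nominal under every rule.

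**3. A second set of assumptions.** This run used a summed class, latent correlation 0.5, education HR 1.11 / 1.16 / 1.22 and literacy OR 1.65 / 2.2 / 3.0 per level. The spurious HR was 1.003 / 1.015 / 1.047 with class only, and 0.999 / 0.997 / 1.007 once education was added. With SE = 1/√(1,500 × 0.243) = 0.052, the class-only values give false-positive rates of about 5%, 6% and 14%. So a summed class is not safe under every input. This SE ignores the precision lost by adjustment, so the rates are slightly high.

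**4. Scale against the target.** Incidences of 60% and 66% correspond to HR = ln(0.34)/ln(0.40) = 1.0788/0.9163 ≈ 1.18. This is a conversion made here under proportional hazards; the article states no HR. On the log scale the two largest spurious HRs are ln 1.062/ln 1.177 = 0.0602/0.163 ≈ 37% and ln 1.067/ln 1.177 = 0.0649/0.163 ≈ 40% of it.

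**The case against.** The strongest reply is that education is already adjusted for through the class, and that the coding of a composite is commonly left to a full protocol or analysis plan behind a condensed article. The article never says that education is used for nothing else. The explicit list belongs to the baseline models, whereas the morbidity Cox models point to a wider set with employment, income and housing items. Those could absorb much of what the class leaves behind, and neither simulation included them. The literature cited on literacy regardless of education concerns lifestyle behaviours, not morbidity, and commits the plan to no covariate set.

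Most of this limits the size of the point. For the Cox models the absence of an education term is the natural reading, not an explicit statement. For the baseline models it is written out, and that list also leaves out income and housing. The covariate set is stated and education is given a specific role in it, so this is a choice in the text and not silence.

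A reader might infer that the literacy test will reject too often. The documents do not support that: they give neither the class rule nor the size of education's effect, and several plausible combinations show no inflation. A reader might also set a spurious HR of 1.07 against the planned relative risk of 1.1 and call it most of the effect. That compares different scales; on a common one the share is about 40% in the worst case simulated.

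**Conclusion.** The point holds as a risk of residual confounding, of minor severity. As written, education enters only through occupational social class: explicitly in the baseline multilevel models, and by the natural reading in the Cox models. The class-only literacy estimate may therefore carry part of the effect of education.

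Under the main assumed inputs, type I error is close to nominal (about 4 to 6%) when the class keeps most of the information on education. It is about 9 to 18%, with a spurious HR of about 1.03 to 1.07, when the class is coarse or mainly occupational and education has an HR of 1.15 to 1.20 per level; at 1.10 it is 7 to 8%. The more extreme second set of inputs gives 14% even with a summed class. All these figures rest on assumed associations and leave out income, employment and housing adjustment. The sample size and every other stated figure stand.

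**What to change.** In the health-literacy models, both Cox and baseline multilevel, enter educational level in three or four categories as its own covariate, with occupation or occupational class as a separate term. Report the class-only model as a sensitivity analysis, and state the rule by which the class is formed.

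Education has to be collected to build the class, so no new data are needed. The cost is two or three degrees of freedom against roughly 1,300 to 1,500 expected events (0.60 × 2,158 ≈ 1,295 at the lower end) and a slightly wider interval for health literacy. If the composite is kept beside education, its coefficient becomes harder to interpret, because it already contains education; using occupation alone avoids this. The calculations concern health literacy only, so they do not by themselves require the change in the models for the other five aptitudes.

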### Data collection process

2.5.

Once the project has been approved by the pertinent ethics committees, informative meetings will be held at the PHC centers to explain the project to health professionals so they can address any questions that may arise. Subsequently, assigned personnel (may vary according to the AACC) will be asked to prepare a list with the people ascribed to the PHC center who meet the inclusion criteria of the study and make a random selection of the necessary sample, oversampling by 30%, in order to be able to substitute participants that should be excluded. In some PHC centers, professionals will directly call possible participants to invite them to be included in the study. In other centers, permission will be requested from the professionals so that a person linked to the study makes the calls on their behalf in a centralized manner.

Participants recruitment: a letter will be sent by mail to the candidates with the study information sheet and 10 self-administered questionnaires: (1) the self-efficacy scale; (2) the resilience scale; (3) level of physical activity; (4) quality of life; (5) the sleep quality index; (6) a disability assessment; (7) occupational stress; (8) stressful life events; (9) the functional social support questionnaire; and (10) the SOGI questions. This letter will be sent to participants before or after the phone contact, as decided by each AACC. The person in charge of calling the participants will invite them to participate in the study and schedule a day and time to attend their PHC centers. If they accept, they will be asked to fill out the self-administered questionnaires and deliver them to a nurse at the PHC.

During the face-to-face visit, the person will be invited to sign the informed consent and clarify doubts, if any, about the information sheet and the study in general. In a confidential sheet, separate from the rest of the variables, the name, surnames, postal address, and contact telephone numbers will be recorded. A case identification number will be given. Study data will be collected and managed using REDCap (93, 94) electronic data capture tools hosted at *Fundació Institut Universitari per a la recerca a l’Atenció Primària de Salut Jordi Gol i Gurina* (IDIAPJGol).

During the visit, participants will be invited to answer the questionnaires and the physical examination will be performed. The information collected in the self-administered questionnaires will be reviewed; if someone has not been able to fill them out, they will do it during the visit. On this first visit, a fasting blood sample extraction will be scheduled to determine (on a second visit) the parameters explained before. Finally, a letter with the examination results will be sent to each participant to allow consultation with the professionals from their health center if any abnormalities were detected. Figure 2 shows the data collection process with the actions that will affect the participants included in the study.

**Figure 2 fig2:**
[figure not shown]
Data collection process with the actions that will affect the participants included in the study.

### Statistical analysis

2.6.

The statistical analysis will include a descriptive analysis. Percentages of the categorical variables will be calculated for each AACC. Continuous variables with a normal distribution will be described with the mean (standard deviation, SD); otherwise, the median (first and third quartile) will be used. The analyses will be stratified by sex. Bivariate analyses will be performed using the *t*-test for independent samples, or the Mann–Whitney test when required, to analyze continuous variables; and the Chi-squared test for proportions.

Objective one will analyze the incidence of morbidity, defined as the onset of any new condition out of the 17 considered. To this end, a Cox model will be built for each independent variable, and adjusted for the above-mentioned covariates. Potential heterogeneity between AACC will be estimated by introducing random effects in the model. Sensitivity analyses will examine loss to follow-up rates. Objective two will analyze the incidence of the rest of the dependent variables (except incidence of morbidity) using also Cox models, one for each of the six independent variables, adjusted for the covariates. We will calculate the incidence of all-cause mortality and its Kaplan–Meier, stratified by the categorical variables and AACC. Potential heterogeneity will be estimated, and sensitivity analyses performed as in objective one.

Before obtaining the follow-up information at 5 and 10 years, we will describe and analyze the gathered data at baseline. To this end, general linear multilevel models will be used to examine the association of the dependent variables (lifestyles, quality of life, and use of services), with the six independent variables, adjusted for the registered covariates (age, sex, occupational social class, social capital, functional capacity, and stress level). Potential disparities between AACC will be captured by including random effects in the models.

Statistical significance will be considered at *p*-values < 0.05. The analyses will be carried out using the Statistical Package for the Social Sciences (SPSS) version 26.0, and the R-software.

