**Methods:**

This protocol addresses the quantitative branch of a multicenter project (10 teams) for the creation of a cohort of at least 3,083 persons aged 35 to 74 years from 9 Autonomous Communities (AACC). The personal variables to evaluate are self-efficacy, activation, health literacy, resilience, locus of control, and personality traits. Socio-demographic covariates and social capital will be recorded. A physical examination, blood analysis, and cognitive evaluation will be carried out.

Several sets of six Cox models (one for each independent variable) will analyze the incidence of morbidity (objective 1); all-cause mortality and the rest of the dependent variables (objective 2). The models will be adjusted for the indicated covariates, and random effects will estimate Potential heterogeneity between AACC.

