### Study objectives and hypotheses

1.1.

This project was designed as a hybrid study, composed of a quantitative part (exposed in this article) and a qualitative part (published in another article).

The quantitative part of the DESVELA cohort has the following objectives:

To analyze whether personal aptitudes related to certain behaviors (self-efficacy, activation, health literacy, resilience, locus of control, and personality traits) are independently associated with the incidence of morbidity.To analyze whether personal aptitudes related to certain behaviors (self-efficacy, activation, health literacy, resilience, locus of control, and personality traits) are independently associated with lower all-cause mortality, improved engagement in healthy lifestyles, higher quality of life, and lower utilization of the health services during follow-up.

We hypothesize that personal aptitudes that are related to positive behaviors (a higher self-efficacy, activation, health literacy, resilience, an internal locus of control, and positive personality traits) will be independently associated with a lower incidence of morbidity. We also hypothesize that personal determinants related to positive behaviors (a higher self-efficacy, activation, health literacy, and resilience, an internal locus of control, and positive personality traits) will be independently associated with all-cause mortality, engagement in healthy lifestyles, higher quality of life, and more optimal use of the health services during follow-up.

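### Each planned Cox model holds one aptitude only, so none can show that an aptitude is associated with outcome independently of the other aptitudes

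*Protocol article*

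**What the plan says.** Under Study objectives and hypotheses, objective 1 asks whether self-efficacy, activation, health literacy, resilience, locus of control and personality traits "are independently associated with the incidence of morbidity". The hypothesis is that the favourable form of each "will be independently associated with a lower incidence of morbidity". Objective 2 uses the same adverb for mortality, lifestyles, quality of life and service use. The article does not say what the association is to be independent of.

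The model structure is stated three times:

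- Abstract, Methods: "Several sets of six Cox models (one for each independent variable) will analyze the incidence of morbidity (objective 1".
- Statistical analysis, objective 1: "a Cox model will be built for each independent variable, and adjusted for the above-mentioned covariates".
- Statistical analysis, objective 2: "one for each of the six independent variables, adjusted for the covariates".

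The Variables section defines the adjustment set: "we will consider the following groups of covariates: sociodemographic, social, functional capacity, and stress level". Table 1 lists aptitudes and covariables under separate headings. For the baseline cross-sectional models the article is more specific: "adjusted for the registered covariates (age, sex, occupational social class, social capital, functional capacity, and stress level". No aptitude appears in either list.

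**The concern.** The word in the objectives and the structure of the models may not match. If two aptitudes are correlated after the covariates are accounted for, an aptitude modelled alone picks up part of the other's association. Some overlap is plausible from the article's own Introduction. It defines self-efficacy as confidence in managing stressors and resilience as positive adaptation to stress. Activation and health literacy are both described through the ability to look after one's own health.

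The consequence is practical. The Introduction and Conclusion look ahead to interventions that improve particular modifiable aptitudes, with health literacy named as an example. If several aptitudes are reported as independent determinants when one carries the association, an intervention may be aimed at the wrong one.

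**Working it through.** **1. The plan's own figure.** Inputs from Sample size: about 60% morbidity, RR 1.1 at 10 years (so 60% against 66%), two-sided alpha 0.05, 80% power, 30% loss, 1,793 exposed and 1,290 non-exposed (ratio 1.39). Taking the 60% as the non-exposed risk, the two-proportion formula with continuity correction gives 900 + 1,251 = 2,151, and 2,151 / 0.70 = 3,073 against the stated 3,083. The sample size reproduces to within 3% and is not in dispute.

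**2. Information available.** 3,083 × 0.70 = 2,158 completers. At 60%, 0.60 × 2,158 ≈ 1,295 events. The standard error of a log HR per SD is about 1/√1,295 = 0.0278.

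**3. What a null aptitude shows when modelled alone.** Let aptitude A have a log HR of β per SD. Let B have no effect of its own and correlate ρ with A after the covariates. Modelled alone, B shows a log HR of about ρβ. The article gives no correlations, so ρ is assumed. Two values of HR for A are shown, coded as protective (1/1.1 = 0.909 and 1/1.2 = 0.833).

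Worked case, A = 1.1, ρ = 0.3: ρβ = 0.3 × ln 1.1 = 0.0286; z = 0.0286 / 0.0278 = 1.03; chance of p < 0.05 about 18%.

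Simulated Cox models (n = 2,158, 60% events at 10 years, 1,000 replicates per setting):

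| HR of A per SD | ρ | HR of B alone | B alone, p < 0.05 | B with A in model, p < 0.05 |
|---|---|---|---|---|
| 1/1.1 | 0.1 | 0.989 | 7% | 4.5% |
| 1/1.1 | 0.3 | 0.972 | 18% | 6.0% |
| 1/1.1 | 0.5 | 0.955 | 36% | 5.0% |
| 1/1.2 | 0.1 | 0.982 | 10% | 4.3% |
| 1/1.2 | 0.3 | 0.948 | 47% | 4.1% |
| 1/1.2 | 0.5 | 0.914 | 90% | 5.3% |

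With A in the model, the HR of B is 1.00 to within 0.002 in every row.

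**4. Which effect size is nearer the plan's.** Risks of 60% and 66% correspond to a between-group HR of ln(0.34)/ln(0.40) = 1.18. If the score is normal and split at 58%, the group means lie about 1.6 SD apart, so ln(1.18)/1.6 ≈ 0.10, or an HR of about 1.1 per SD. The upper rows are therefore the ones close to the design effect; an HR of 1.2 per SD is a larger assumption.

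**5. Cost of mutual adjustment.** The variance is inflated by 1/(1 − ρ²). Dividing the 903 non-exposed completers (1,290 × 0.70) by this factor, with the exposed in proportion, power for RR 1.1 (no continuity correction) is 81% at ρ = 0, 81% at 0.1, 78% at 0.3 and 70% at 0.5. With all aptitudes in the model, ρ² is replaced by the R² of one aptitude on all the others, which cannot be smaller than any single ρ².

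**The case against.** The strongest reply is about meaning. The objective asks whether the aptitudes are independently associated, not which of them are, and in cohort reports the adverb often means after adjustment for the listed covariates. On that reading objective and models agree. This stands as a possible reading, but the article does not state it, and its interest in acting on particular aptitudes calls for more.

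The covariates are also not merely demographic. They include social capital, social support, disability, threatening life events and occupational stress. Only the correlation left after these matters, and it may be small; at 0.1 the borrowing is slight.

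The baseline cross-sectional models are worded as relating outcomes to the six aptitudes and may be joint. A reader might infer that no planned model of any kind holds more than one aptitude; the text does not support that. What can be said is that no planned Cox model does, and the baseline models do not address incident morbidity.

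A joint model is not simply better. If personality acts through self-efficacy, for example, mutual adjustment removes part of its total association.

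Finally, an article may leave supplementary models to an analysis plan. Here, however, the article itself fixes the structure of the Cox models, and that structure does not support the broader sense of the word.

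**Conclusion.** The point holds. As planned, the Cox models can show association independent of the listed covariates, but not of the other aptitudes. Under an assumed residual correlation of 0.1 to 0.5, a null aptitude would be declared significant in about 7% to 36% of studies if its correlate has an HR of 1.1 per SD, and in about 10% to 90% at 1.2, against about 5% with mutual adjustment. These ranges rest on assumed correlations and effects and on a two-aptitude model.

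Two stronger inferences should be resisted. The first is that false attribution is likely in this cohort: the high percentages need both the larger effect and a sizeable correlation, and the article documents neither. The second is that the single-aptitude models are wrong and that only a joint model may carry the word *independently*. The two kinds of model answer different questions, and the article's causal framing gives a reason to want both.

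**What to change.** - Keep the six single-aptitude Cox models and describe them as total associations, adjusted for the covariates.
- Prespecify one additional Cox model per outcome with all aptitude scores (self-efficacy, activation, resilience, health literacy, locus of control and the Big Five traits) plus the same covariates, where event numbers allow.
- Check events first for all-cause mortality, for which the article gives no expected count, and for any analysis stratified by sex, which divides the events.
- Report both sets of estimates side by side, with the correlations between aptitudes.
- State for each result whether *independently* means of the covariates only or also of the other aptitudes.

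The cost is one more model per outcome on data already collected at baseline. The joint estimates will be less precise: the sample was sized for health literacy alone, with no allowance for correlated exposures. They also exclude any effect that runs through another aptitude, so they should be read beside the single models and not replace them.
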